To evaluate the effects of amblyopia treatment in the control and VR app groups, BCVA in the amblyopic eye will be assessed as secondary outcome 1 and stereopsis in the amblyopic eye as secondary outcome 2. To assess the reliability and validity of stereopsis measurement using the VR app, secondary outcome 3 will involve comparing stereopsis in the amblyopic eye measured using the VR app for pediatric amblyopia with that obtained during clinical visits using the Titmus stereo test. To evaluate treatment adherence in the control and VR app groups, secondary outcome 4 will involve assessing the ratio of the total wearing time to the target wearing time. To evaluate the safety of amblyopia treatment using the VR app, secondary outcome 5 will involve comparing the angle of strabismus in the amblyopic eye between the control and the VR app groups. To investigate how VR gameplay status correlates with efficacy and safety, secondary outcome 6 will involve examining the VR gameplay status in the VR app group (including game type, play date or time, play duration, and game settings) in relation to BCVA, stereopsis, treatment adherence, and ocular deviation. Secondary outcome 7 will evaluate malfunctions of the VR app for pediatric amblyopia, secondary outcome 8 will monitor adverse events, and secondary outcome 9 will assess usability in the VR app group. Adverse events will be monitored throughout the trial. Based on our safety evaluation of the VR app in adults, where no visually induced motion sickness (VIMS) or vision-related adverse events occurred [18], the intervention is not expected to pose major safety concerns. However, careful monitoring remains essential in pediatric populations. Possible adverse events include VIMS, asthenopia, diplopia, transient blurring, and headaches. All adverse events reported by participants or observed during clinic visits will be documented and evaluated for severity and relationship with the intervention. Among the secondary outcomes, those related to BCVA, stereopsis, ocular deviation, and treatment adherence (secondary outcomes 1‐4) have been defined as key secondary end points. Since this is an exploratory clinical study, all secondary outcomes other than the primary outcome will be analyzed and interpreted in an exploratory (hypothesis-generating) manner.

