### Sample Size and Statistical Analyses

The primary outcome of this study will be to determine whether the improvement in BCVA from enrollment to 12 weeks in the VR app group is noninferior to the improvement in BCVA from enrollment to 12 weeks in the control group. Based on the assumption that the difference in mean BCVA at 12 weeks between the control and VR app groups will be 0.07 LogMAR [35], the common standard deviation will be 0.14 [36] LogMAR, the noninferiority margin will be 0.10 LogMAR [37], the significance level will be 2.5%, and statistical power will be 90%, a sample size of 24 participants (12 per group) is required [19]. Anticipating a dropout rate of approximately 20%, the target sample size has been set to 30 participants (15 per group).

To assess whether the VR-based program for amblyopia is noninferior to eye patch therapy, the 95% CI for the change in BCVA between 0 and 12 weeks will be calculated for both the control and VR app groups. If the lower bound of the 95% CI for the change in BCVA in the VR app group is greater than that in the control group, the VR-based program for amblyopia will be considered noninferior to eye patch therapy, and the primary outcome criterion will be met.

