For between-group comparisons of BCVA, stereopsis, ocular deviation, and the ratio of total treatment time to the target treatment time, 2-tailed *t* tests or repeated-measures mixed-effects models will be used. Within-group comparisons will be conducted with 2-tailed paired *t* tests, repeated-measures analysis of variance, or repeated-measures mixed-effects models. Reliability and validity evaluations of stereopsis measurements using the VR app compared with the Titmus stereo test administered at clinical visits will be performed using 2-tailed paired *t* tests, Cronbach α coefficients, or intraclass correlation coefficients. The associations between VR gameplay status, ophthalmological examination results, and treatment adherence will be examined using multiple regression analyses or mixed-effects models adjusted for confounding factors. The number of adverse events in the control and VR app groups will be compared using the chi-square test. If continuous variables deviate substantially from a normal distribution, more appropriate methods such as the Mann-Whitney *U* test will be applied. A 2-sided significance level of 5% (*P*<.05) and 95% CI will be used for all analyses. We will not apply multiplicity adjustments across secondary outcomes that represent different endpoint domains. However, when repeated measurements of the same outcome are compared at multiple time points (eg, longitudinal analyses of BCVA), appropriate multiple-comparison adjustments (eg, Bonferroni correction or equivalent family-wise error control) will be applied within that end point family. Primary and secondary analyses will follow intention-to-treat, including all data collected before withdrawal. A per-protocol analysis will be performed as supplementary to assess the robustness of the findings.

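### The family-wise correction for repeated measurements has no safety exemption, so it also covers the strabismus-angle safety comparison and makes harm harder to flag in a test that is already weak

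*Protocol article*

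**What the plan says.** Four statements in the protocol article bear on this point.

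- **Purpose of the outcome.** Secondary Outcomes: "To evaluate the safety of amblyopia treatment using the VR app, secondary outcome 5 will involve comparing the angle of strabismus in the amblyopic eye". The list in the same section sets this comparison at baseline and at weeks 4, 8, 12, 16, 20 and 24.
- **The multiplicity rule.** Sample Size and Statistical Analyses applies it "when repeated measurements of the same outcome are compared at multiple time points (eg, longitudinal analyses of BCVA"), and then "appropriate multiple-comparison adjustments (eg, Bonferroni correction or equivalent family-wise error control) will be applied within that end point family". BCVA is an example of an outcome and Bonferroni an example of a method. No outcome is excluded. Across different endpoint domains there is no adjustment.
- **The test.** For ocular deviation, among others, "2-tailed *t* tests or repeated-measures mixed-effects models will be used".
- **The level and the interval.** "A 2-sided significance level of 5% (*P*<.05) and 95% CI will be used for all analyses".

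The only margin in the article is for BCVA. None is given for strabismus angle. Secondary outcomes are described as exploratory.

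**The concern.** Family-wise control limits the chance of at least one false positive. That suits a set of efficacy comparisons, where the error to guard against is a false claim of benefit. For a safety comparison the more serious error is missing a real worsening, and a stricter threshold makes that error more likely. If baseline is counted as a seventh comparison, part of the allowance also goes to a test in which randomisation makes any difference due to chance.

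At stake is what the trial can say about ocular alignment in children aged 3 to 10. With 12 to 15 children per arm, a non-significant adjusted result at any given visit is the likely outcome even if alignment has worsened, so it carries little information.

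**Working it through.** **Inputs from the article**

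- Group size: "a sample size of 24 participants (12 per group) is required", and "the target sample size has been set to 30 participants (15 per group"). I use 12 and 15 per arm.
- Comparisons in the family: six post-baseline visits, or seven if baseline is tested.
- Two-sided level 5%, so Bonferroni gives 0.05/6 = 0.0083 or 0.05/7 = 0.0071.

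**Assumptions of mine.** The worsening under VR is 0.5 SD, with 0.8 and 1.0 SD as a range. The correlation between visits is 0.5 to 0.9. There are no missing data within the n used.

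**The plan's own figures.** The article gives no power for strabismus angle, so only the group sizes can be checked. The dropout step reproduces: 24/0.8 = 30. The 12 per group does not: with a 0.07 logMAR difference in favour of VR, 2 × 0.14² × (1.960 + 1.282)² / (0.10 + 0.07)² = 14.3, so 15 per arm. That is a separate matter; here I take 12 and 15 as the range.

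**Step 1: power at one visit.** For a two-sample t test, the noncentrality is d/√(2/n) on 2n − 2 degrees of freedom.

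- n = 15, d = 0.5: 0.5/√(2/15) = 1.369. Critical t(28) is 2.048 at 0.05, 2.839 at 0.05/6 and 2.902 at 0.05/7.
- n = 12, d = 0.5: 0.5/√(2/12) = 1.225. Critical t(22) is 2.074, 2.899 and 2.966.

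| n per arm | Worsening | Power at 0.05 | Power at 0.05/6 | Power at 0.05/7 |
|---|---|---|---|---|
| 15 | 0.5 SD | 26.2% | 8.8% | 8.0% |
| 15 | 0.8 SD | 56.2% | 28.0% | 26.1% |
| 15 | 1.0 SD | 75.3% | 47.2% | 44.9% |
| 12 | 0.5 SD | 21.6% | 6.6% | 5.9% |
| 12 | 0.8 SD | 46.6% | 20.3% | 18.7% |
| 12 | 1.0 SD | 64.9% | 35.2% | 33.0% |

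**Step 2: how much is due to the correction.** At 0.5 SD and 15 per arm the miss rate goes from 73.8% to 91.2-92.0%, an addition of 17.4 to 18.3 points. At 12 per arm it goes from 78.4% to 93.4-94.1%, an addition of 15.0 to 15.7 points. The small sample accounts for the rest.

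**Step 3: all six visits together.** I simulated a constant 0.5-SD shift at six equally correlated visits (20,000 trials per setting). The table compares the chance that at least one visit passes 0.05/6 with the power of one unadjusted contrast averaged over the visits.

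| n per arm | Correlation | Any visit, Bonferroni | Averaged contrast, 0.05 |
|---|---|---|---|
| 15 | 0.9 | 16% | 28% |
| 15 | 0.7 | 24% | 33% |
| 15 | 0.5 | 30% | 41% |
| 12 | 0.9 | 14% | 23% |
| 12 | 0.7 | 20% | 27% |
| 12 | 0.5 | 24% | 34% |

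**Step 4: width of the interval.** The half-width is t × √(2/n) in SD units. At one visit, an unadjusted 95% CI has half-width 0.75 SD (n = 15) or 0.85 SD (n = 12). At the level 0.05/6 it is 1.04 or 1.18 SD.

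**Step 5: false signals.** The same simulation with no true shift flags at least one visit at 0.05/6 in about 2-4% of trials. The averaged contrast flags about 5%. If each visit were read separately at an unadjusted 5%, at least one would be flagged in about 11-21%.

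**The case against.** The case on the other side is substantial, and much of it limits the point.

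- **An interval is already planned.** 95% CIs are stated for all analyses, so a reader who infers that no upper bound exists for strabismus angle goes too far. What is absent is a limit to set it against, and a statement that safety is read from it.
- **The small sample is the main cause.** This stands. Without any correction the per-visit test already misses 74-78% at 0.5 SD. It would be wrong to blame the correction for the whole miss rate of over 90%.
- **Bonferroni is not fixed, and a mixed model is allowed.** Also true. A single overall group contrast would not be a comparison at several time points and would escape the rule. But the alternative to Bonferroni must give equivalent family-wise control, and the outcome is listed visit by visit, so visit-wise contrasts from a mixed model would still fall under the rule.
- **Nothing says that P>.05 will be read as safety.** Correct; a reader might infer it from a difference test on a safety outcome, but the article does not state it. Safety also does not rest on this outcome alone: adverse events are monitored throughout, and their number is compared by a chi-square test that the rule does not reach.
- **The outcome is exploratory.** This supports the change more than it opposes it, since hypothesis-generating safety data have little need of family-wise control.
- **The baseline may be only a reference.** The list of times can be read that way, so the seven-comparison count is one reading. The results for six and seven differ by about 2 points or less per visit.
- **Such details belong in an analysis plan.** Many do. Here, however, the article itself states a general rule, and as worded it takes in the safety outcome.

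**Conclusion.** The point holds in a limited form. As written, the multiplicity rule reaches the strabismus-angle safety comparison and works in the wrong direction there. If Bonferroni is applied per visit, the chance of flagging an assumed 0.5-SD worsening at a given visit falls to about a third of its uncorrected value; at 0.8 SD it falls to about half or less. For a sustained 0.5-SD shift, one unadjusted averaged contrast would detect about 7 to 12 percentage points more than the corrected visit-by-visit search, over the correlations assumed. It would still miss most such shifts, which is why the interval should carry the safety reading and not the P value.

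The sizes depend on effect sizes and correlations that the article does not supply. The direction does not: for any real worsening, a stricter threshold lowers the chance of detecting it.

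**What to change.** In Sample Size and Statistical Analyses:

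1. Exempt secondary outcome 5 (strabismus angle) from the multiplicity adjustment, and state that no baseline test belongs to its family.
2. Make the main safety estimate one between-group contrast of change from baseline, averaged over weeks 4 to 24, from the mixed-effects model already allowed.
3. Report that contrast and each visit with unadjusted 95% CIs.
4. State that safety is read from the confidence limit on the side of worsening under VR, and that P>.05 is not evidence of no harm.

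No change is needed for adverse events.

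The cost is wording only, with no added patients or data. The chance of a false safety signal rises from about 2-4% to about 5% on the averaged contrast. It would be about 11-21% if each visit were read separately, so the per-visit intervals should be descriptive.

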**Conclusions:**

This study will clarify the effectiveness of the newly developed VR app in improving treatment outcomes and adherence among pediatric patients with amblyopia. By addressing the limitations of conventional occlusion therapy and providing a potentially more efficacious and acceptable treatment option, the VR app may enhance clinical outcomes and represent a paradigm shift in the treatment of pediatric amblyopia.

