This study aims to conduct a multicenter clinical trial to assess the therapeutic effectiveness of a VR app in pediatric amblyopia. The use of the VR app is expected to enable amblyopia training with higher adherence and enhanced efficacy compared to conventional occlusion therapy, with the potential to mitigate the societal burden attributable to pediatric amblyopia.

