### Primary Outcome

The primary outcome measure will be that the improvement in BCVA in the amblyopic eye from enrollment to 12 weeks in the VR app group is noninferior to the improvement in BCVA in the amblyopic eye from enrollment to 12 weeks in the control group. This outcome measure will be designed to confirm that the amblyopia treatment effect of the VR-based program is not inferior to that of conventional eye patch therapy. In addition, since previous studies investigating amblyopia treatment using a VR headset have shown a significant treatment effect following 12 weeks of use, comparing BCVA at 12 weeks will enable an efficacy assessment of the VR-based program for amblyopia under standard amblyopia treatment conditions, and thus, the 12-week time point will be adopted [19,34].

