### Secondary Outcomes

Secondary outcomes are as follows:

Comparison of BCVA in the amblyopic eye at baseline and at weeks 4, 8, 12, 16, 20, and 24 between and within the control group (eye patch for the sound eye) and the VR app groupComparison of stereopsis in the amblyopic eye at baseline and at weeks 4, 8, 12, 16, 20, and 24 between and within the control and VR app groupsIn the VR app group, stereopsis in the amblyopic eye measured using the VR-based program for pediatric amblyopia will be compared with stereopsis measured using the Titmus stereo test at baseline and at weeks 4, 8, 12, 16, 20, and 24 during clinic visitsComparison of the ratio of total wearing time to target wearing time (treatment adherence) at weeks 4, 8, 12, 16, 20, and 24 between the control and VR app groupsComparison of the angle of strabismus in the amblyopic eye at baseline and at weeks 4, 8, 12, 16, 20, and 24 between the control and VR app groupsIn the VR app group, the association between the VR gameplay status (including game type, play date/time, play duration, and game settings) and BCVA in the amblyopic eye, stereopsis, the ratio of total wearing time to the target wearing time, and ocular deviation will be evaluatedMalfunctions of the VR-based program for pediatric amblyopiaAdverse eventsUsability evaluation (VR app group only)

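### A prespecified step from week-12 noninferiority to week-12 superiority in BCVA would cost no alpha; as written, a clear advantage over patching cannot become a planned conclusion

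*Protocol article*

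**What the plan says.** In the protocol article, Primary Outcome, the primary hypothesis is that BCVA improvement to week 12 with the VR app "is noninferior to the improvement in BCVA in the amblyopic eye from enrollment to 12 weeks in the control group". Sample Size and Statistical Analyses repeats this with a 0.10 logMAR margin. It decides the matter by calculating a 95% CI for the change in each arm and comparing the two lower bounds. Nothing there leads on to superiority.

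The only other between-arm look at week-12 BCVA is secondary outcome 1: "Comparison of BCVA in the amblyopic eye at baseline and at weeks 4, 8, 12, 16, 20, and 24 between and within the control group" and the VR app group. For repeated measurements of one outcome, with longitudinal BCVA given as the example, Sample Size and Statistical Analyses states that "appropriate multiple-comparison adjustments (eg, Bonferroni correction or equivalent family-wise error control) will be applied within that end point family". Secondary Outcomes adds that "all secondary outcomes other than the primary outcome will be analyzed and interpreted in an exploratory (hypothesis-generating) manner".

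On ambition, the Introduction says: "The use of the VR app is expected to enable amblyopia training with higher adherence and enhanced efficacy compared to conventional occlusion therapy". The abstract's Conclusions say: "This study will clarify the effectiveness of the newly developed VR app in improving treatment outcomes and adherence among pediatric patients with amblyopia".

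**The concern.** The hope expressed in the Introduction is that the app does better than patching. The confirmatory test asks only whether it is not much worse. The week-12 contrast is then examined a second time, as one member of an adjusted, hypothesis-generating family of visits.

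Suppose the between-arm 95% CI at week 12 lay wholly on the VR side of zero. The plan could report noninferiority, but it has no route by which superiority becomes a planned finding. The exploratory label and the missing step are the main obstacles. The adjustment across visits adds to them, because it can also turn that result into a non-significant one.

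Timing matters. The trial is open-label and the investigator group decides what is reported (Data Management), so a superiority claim added once results are known would be post hoc.

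**Working it through.** **Inputs.** From Sample Size and Statistical Analyses: "the difference in mean BCVA at 12 weeks between the control and VR app groups will be 0.07 LogMAR"; "the common standard deviation will be 0.14" logMAR; margin 0.10; significance level 2.5%; power 90%; 12 per arm evaluable and 15 per arm enrolled. From Secondary Outcomes: six post-baseline visits, or seven listed time points with baseline. Two assumptions are mine because the article does not settle them: the 0.07 favours VR, and the SD of 0.14 applies to the change in BCVA.

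**The plan's own figure.** With 0.07 favouring VR, the distance to the margin is 0.10 + 0.07 = 0.17. Taking 2.5% as one-sided, n per arm = 2 × 0.14² × (1.960 + 1.282)² / 0.17² = 14.3, so 15 evaluable per arm rather than the stated 12. The figure of 12 appears at one-sided 5% with 90% power (11.6, rounded up). That is a separate matter. I show 12 and 15 per arm below so that nothing here hangs on it.

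**Smallest observed difference that counts as significant.** Critical difference = t(1 − α/2, 2n − 2) × 0.14 × √(2/n). The standard error is 0.0572 at 12 per arm and 0.0511 at 15.

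| Level | 12 per arm | 15 per arm |
|---|---|---|
| 0.05, unadjusted | 2.074 × 0.0572 = 0.119 | 2.048 × 0.0511 = 0.105 |
| 0.05/6 = 0.0083 | 2.899 × 0.0572 = 0.166 | 2.839 × 0.0511 = 0.145 |
| 0.05/7 = 0.0071 (baseline counted) | 2.966 × 0.0572 = 0.170 | 2.902 × 0.0511 = 0.148 |

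The band in which the 95% CI excludes zero but the adjusted test fails is therefore about 0.12 to 0.17 at 12 per arm, and about 0.105 to 0.145 at 15. Both lie above the trial's own 0.10 margin.

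**Power for superiority** (noncentral t, two-sided):

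| True difference | n per arm | Unadjusted | /6 | /7 |
|---|---|---|---|---|
| 0.07 | 12 | 21.5% | 6.6% | 5.9% |
| 0.07 | 15 | 26.2% | 8.8% | 8.0% |
| 0.14 | 12 | 65% | 35% | 33% |
| 0.14 | 15 | 75% | 47% | 45% |
| 0.17 | 12 | 81% | 54% | 52% |
| 0.17 | 15 | 89% | 68% | 66% |

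Counting baseline costs at most about 2 points. Almost all the loss comes from placing week 12 in the visit family at all.

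**Alpha cost of the sequence.** If a 95% CI for the between-arm difference lies above 0, it also lies above −0.10. The two tests are nested, so testing superiority only after noninferiority needs no adjustment. In 400,000 simulated trials at a true difference of zero, the superiority step passed 2.5% of the time on the VR side, at both sample sizes.

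**The gate must be valid.** The current rule has no between-arm interval and does not use the margin. Simulated at a true deficit of 0.10, it passes 5.5% of the time (12 per arm) or 3.5% (15 per arm) instead of 2.5%. At no difference it passes 50%. A sequence cannot be attached to that rule as it stands.

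**The case against.** The strongest reply is that nothing is wrong. The Introduction only expects better efficacy, Secondary Outcomes calls the study exploratory, and the Discussion leaves confirmation to later trials. Testing noninferiority and leaving superiority exploratory is consistent with all of that, and a superiority step is optional. This stands. A reader might infer that the trial promises to show better efficacy and then makes this impossible, but the text does not go that far.

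It is also fair that Bonferroni is only an example. Another family-wise method is allowed and could lose less, and the adjustment does control error across visits. No section fixes the size of the family. Secondary outcome 1 lists baseline, but the statistics section does not say that the baseline comparison counts. A reader might add the within-arm comparisons and infer a much stricter level; the text gives no basis for that count.

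A large advantage could still reach adjusted significance (52% to 68% of the time at a true 0.17), although it would remain hypothesis-generating. At the planned 0.07, the change leaves superiority power low, and 80% would need 63 per arm.

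What these replies do not remove is that the improvement is free and must be prespecified to be usable.

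**Conclusion.** This is a free improvement, not a contradiction or an error. As written, no week-12 BCVA result can be a planned superiority conclusion. For observed differences of about 0.12 to 0.17 logMAR at 12 per arm, the adjusted comparison would also be reported as non-significant, if Bonferroni over six or seven comparisons is used. The gain is material if the true effect is near 0.14 (about 65% against 35% at 12 per arm) and modest at the planned 0.07 (about 22% to 26% against 6% to 9%). These figures rest on an SD of 0.14 for the change, on 0.07 favouring VR, and on Bonferroni as the adjustment. The no-cost argument also requires that the primary rule first be replaced by a valid margin-based test.

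**What to change.** 1. In Sample Size and Statistical Analyses, base the primary analysis on a single between-arm 95% CI for the difference in BCVA change to week 12, compared with the 0.10 logMAR margin. Then state that, if noninferiority is met, superiority at week 12 is tested from that same interval at two-sided 5%.
2. In the multiplicity paragraph, take two comparisons out of the adjusted between-arm BCVA family: week 12, already tested in the primary sequence, and baseline, which is not a treatment comparison. Weeks 4, 8, 16, 20 and 24 remain.
3. In the abstract's Conclusions, make any claim of improved outcomes relative to patching conditional on the superiority step.

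The cost is a few sentences before database lock. No patients, visits or data are added, and the superiority step spends no alpha. The primary decision rule does change, which is needed for the sequence to be valid, and the wording of the conclusion becomes conditional.
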